**7.4 Withdrawal of individual subjects**

Subjects can leave the study at any time for any reason if they wish to do so without any consequences. The investigator can decide to withdraw a subject from the study for urgent medical reasons.

**7.5 Replacement of individual subjects after withdrawal**

A total of 850 patients are needed to receive CGA, individual care plan and follow-up during one year to obtain sufficient power. After correction for 40% drop-out (see Figure p.14), around 1418 participants are needed to enrol in the CGA.

**7.6 Follow-up of subjects withdrawn from treatment**

If the study subject withdraws from study participation, he or she will be receiving geriatric consultation visits as part of the usual provided patient care. Follow-up will take place by telephone.

**7.7 Premature termination of the study**

As the intervention is directed towards improving care provided to elderly people, it appears unlikely that the study will be terminated prematurely.

8.0 SAFETY REPORTING

**8.1 Section 10 WMO event**

In accordance to section 10, subsection 1, of the WMO, the investigator will inform the subjects and the reviewing accredited METC if anything occurs, on the basis of which it appears that the disadvantages of participation may be significantly greater than was foreseen in the research proposal. The study will be suspended pending further review by the accredited METC, except insofar as suspension would jeopardise the subjects’ health. The investigator will take care that all subjects are kept informed.

**8.2 Adverse and serious adverse events**

Adverse events are defined as any undesirable experience occurring to a subject during the study, whether or not considered related to the experimental treatment (For example, an adverse event can also be related to a diagnostic procedure or to an already existing condition)*.* All adverse events reported spontaneously by the subject or observed by the investiga­tor or his staff will be recorded, or reported by the Healt Care Nurse or GP. Mortality and hospital admission rates will be monitored in both conditions and reported to the METC at regular intervals or immediately if necessary.

A serious adverse event (SAE) is any untoward medical occurrence or effect that at any dose:

- results in death;
- is life threatening (at the time of the event);
- requires hospitalisation;
- results in persistent or significant disability or incapacity;
- is a congenital anomaly or birth defect;
- is a new event of the trial likely to affect the safety of the subjects, such as an unexpected outcome of an adverse reaction, lack of efficacy of an IMP used for the treatment of a life threatening disease, major safety finding from a newly completed animal study, etc.

All SAEs will be reported through the web portal *ToetsingOnline* to the accredited METC that approved the protocol, within 15 days after the sponsor has first knowledge of the serious adverse reactions.

SAEs that result in death or are life threatening should be reported expedited. The expedited reporting will occur not later than 7 days after the responsible investigator has first knowledge of the adverse reaction. This is for a preliminary report with another 8 days for completion of the report.

**8.3 Follow-up of adverse events**

All adverse events will be followed until they have abated, or until a stable situation has been reached. Depending on the event, follow up may require additional tests or medical procedures as indicated, and/or referral to the general physician or a medical specialist.

**8.4 Data Safety Monitoring Board (DSMB)**

Due to the minimal expected side effects related to the intervention a DSMB will not be instituted.

9. STATISTICAL ANALYSIS

Statistical analyses will be based on an intention-to-treat principle. Baseline assessments and outcome parameters will be summarized using simple descriptive statistics. The main analysis focuses on a comparison of patients with a similar risk profile (based on ISAR-PC and Katz-ADL scores in both groups). As the Katz-ADL data will have a correlated multilevel structure (patients are ‘nested’ within their GPs) difference between these scores will be analyzed using a linear mixed, multilevel model. If necessary, we will adjust the effect size for baseline imbalance. The same (linear and logistic) multi-level approach will be used with regard to the secondary outcome parameters, including survival rates. Survival data will be additionally analyzed using Kaplan-Meier survival curves and the log-rank test.

We will perform a predefined subgroup analysis for patients with baseline ‘high’ and ‘low’ risk scores (ISAR-PC≥2,5 and less, based on pilot-assessments) on all primary and secondary outcomes. In all analyses statistical uncertainties will be quantified via corresponding 99% confidence intervals.

Finally, process outcome data will be analyzed qualitatively within the theoretical framework of the adaptive implementation model (Meiland 2005).

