3. OBJECTIVES

#### Primary Objective

To prevent functional decline in community-dwelling elderly people of 70 years and older.

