**4.2 Inclusion criteria**

Phase 1 (general screening):

- Patients aged 70 years and older

Phase 2 (intervention)

- An increased risk for functional decline, defined as a score of two or more on the ISAR-PC screening instrument
- Speaks and understands Dutch
- Patient is registered with a GP

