**Total population ≥70 yrs**

**n=8220**

**Baseline measurement**

**n=5670**

**Increased risk: ±50%**

**Invitation for CGA**

**n=1418 (100%)**

**CGA**

**n=1134 (80%)**

**Intervention: 10/11 GP practices; N≈2835**

**Exclusion (6%, n=658):**

- Restricted life expectancy

- Dementia

- Planning to move

- Unable to speak Dutch

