7. METHODS

**7.1 Study parameters/endpoints**

The primary outcome measure is the level of (instrumental) activities of daily living (baseline-12 months), measured with the modified Katz ADL index (15 items).

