**7.3 Study procedures**

| **Measures** | **Intervention group** | **Control group** |
| --- | --- | --- |
| **<4 wks,** Extractions from electronic medical records (in Dutch: Huisarts Informatie Systeem, HIS) by GP of all patients aged 70 and over.  Screening for eligibility by GP (inclusion criteria). | **X** | **X** |
| **<2 wks** Pre-randomisation at the level of GP practices | **X** | **X** |
| **Start of study (Sept. 2010):**  Postal questionnaires (i.e. ISAR-PC, Katz-ADL, MDS), along with study information and postponed informed consent | **X** | **X** |
| **6 wks**  -Comprehensive Geriatric Assessment: (CGA; Appendix 2).  -Integrated care and treatment plan, discussed with both patient and GP  -Start of implementation care and treatment plan; follow-up contact with practice nurse (and other care givers if indicated) is planned | **X** |  |
| **6 wks – 12 months***  Follow-up contacts (7) by nurse to monitor the care and treatment plan | **X** |  |
| **6-12-18-24 months**  Postal questionnaires containing KATZ-(I)ADL, ALDS (T0/T12) and MDS. | **X** | **X** |

*** Total recruitment period will take around 6 months; therefore, the last GP practices included will end 6 months later than the first.**

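### Section 9 ties the main comparison to ISAR-PC and Katz-ADL scores, but the at-risk population is defined by ISAR-PC alone and the Katz part has no rule

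*Protocol*

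**What the plan says.** Section 9 opens with "Statistical analyses will be based on an intention-to-treat principle". Shortly afterwards it describes the main comparison: "The main analysis focuses on a comparison of patients with a similar risk profile (based on ISAR-PC and Katz-ADL scores in both groups". It then names a multilevel linear mixed model for the Katz scores and makes adjustment for baseline imbalance conditional on need.

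Section 4.2 sets the risk criterion for the intervention phase: "An increased risk for functional decline, defined as a score of two or more on the ISAR-PC screening instrument". Neither section 4.2 nor the exclusions in section 4.3 mention Katz. The flow chart in section 5 goes from about 2835 people per arm to 1418 invited for assessment, through a box labelled "Increased risk: ±50" per cent, and has no Katz step.

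Section 7.1 makes the same scale the primary outcome: "The primary outcome measure is the level of (instrumental) activities of daily living (baseline-12 months", measured with the 15-item modified Katz index. The table in section 7.3 lists "Pre-randomisation at the level of GP practices" first and then, at the start of the study in both arms, "Postal questionnaires (i.e. ISAR-PC, Katz-ADL, MDS), along with study information and postponed informed consent".

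**The concern.** A protocol should let a reader decide, from one patient's baseline form, whether that patient belongs to the primary analysis. Here the entry rule gives one answer and the analysis section adds a second variable without saying how it works. A patient with an ISAR-PC score of 2 or more and a very high or very low Katz score clearly meets section 4.2. Whether the same patient counts in the main comparison cannot be read from section 9.

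Katz is the outcome scale, so any selection on it changes which part of the outcome distribution is studied. Similarity between groups is also a property of the two arms together, and both scores arrive after the practices have been allocated. If the sentence were used to select, the result might no longer describe the section 4.2 population, and the composition of the set would depend on a choice that the protocol does not fix.

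**Working it through.** This is a question of text, so the main check sets the places side by side.

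| Place in the protocol | Who is meant | ISAR-PC | Katz-ADL |
|---|---|---|---|
| Section 4.2, phase 2 | People entering the intervention phase | 2 or more | Not mentioned |
| Section 4.3 | Exclusions | Not mentioned | Not mentioned |
| Section 6, step 2a | People who go on to assessment | 2 or more | Not mentioned |
| Flow chart, section 5 | At-risk group | About 50% of respondents | No step |
| Section 9, main analysis | Patients alike in risk in both groups | Named, no cut-off | Named, no cut-off, time point not given |
| Section 9, subgroups | High and low risk | Split at 2.5 | Not mentioned |

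**Flow-chart count.** Respondents with a baseline measurement: 5670 (flow chart). Per arm at 1:1 allocation: 5670 / 2 = 2835, as the chart states. At-risk share of about 50%: 2835 × 0.50 = 1417.5, or about 1418, again as the chart states for the intervention arm. The printed 1418 is therefore reached from the increased-risk share alone, with nothing taken off for Katz. The chart prints no at-risk count for the control arm. About 1418 there is an assumption that the same 50% applies.

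**Order of events.** In section 7.3 practices are pre-randomised first, then the questionnaires with ISAR-PC and Katz-ADL go out, and the geriatric assessment follows at 6 weeks. Two things follow:

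- Any judgement of similarity between arms on these scores must come after allocation.
- The baseline scores precede the assessment, so a fixed rule on them, applied identically in both arms, would be legitimate.

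**Two readings of the sentence.**

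1. *Selection.* Patients count only if they are alike on both scores. This needs a cut-off, tolerance or matching rule, and none is given. The set then differs from section 4.2.
2. *At-risk against at-risk.* At-risk intervention patients are compared with at-risk controls. ISAR-PC of 2 or more, collected in both arms, does this by itself, and Katz adds nothing to the definition. Using Katz as a covariate is a matter of adjustment, which section 9 covers in a separate, conditional sentence.

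The first reading conflicts with the entry rule. The second leaves the mention of Katz without a function.

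**Loss of patients.** No number can be derived. It would need a Katz rule and a baseline Katz distribution, and the protocol gives neither.

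**The case against.** The best defence is that the sentence is loose wording for something sensible. Everyone aged 70 or older in both arms gets the questionnaire, but only at-risk people in intervention practices are invited for assessment. The analysis therefore has to say that the comparator is at-risk controls and not all controls. Section 7.2 uses the term risk profile for the screening result. Section 9 describes no matching, trimming or exclusion step, and a provision to adjust for baseline imbalance would be largely redundant after matching on Katz. All of this stands, and it makes the second reading plausible. It does not explain why Katz is named.

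A second defence is that analysis sets are commonly detailed in a statistical analysis plan, which is not at hand. That is true of detail. But here the protocol itself states the main comparison in terms that do not agree with its own entry rule, and it does give a numeric cut-off for the subgroups.

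A reader might go further and infer that the sentence breaches the intention-to-treat principle declared just before it, or that randomisation no longer protects the comparison. The text does not support that. Restricting by a baseline characteristic under a fixed rule, the same in both arms, defines a population and still analyses people as allocated. The protection would be lost only if the rule differed by arm or were chosen with outcomes in view, and section 9 says neither.

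**Conclusion.** The point holds as a conflict between stated populations and as an undefined role for the outcome scale. Section 9 names Katz-ADL in defining the main comparison. Section 4.2 and the flow chart do not, and the sentence leaves both the time point and the rule open. This is worth correcting before outcome data are examined, because it concerns who is in the primary analysis.

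The set at issue is about 1418 people per arm, assuming an equal at-risk share in both arms. How many of them a Katz condition would remove, and in which direction the estimate would move, cannot be given from the documents. A reader might put a percentage on the loss or infer an inflated false-positive rate. Either would rest on invented Katz windows and, for the error rate, on an outcome-driven choice that the protocol does not describe. The conclusion rests on the wording alone and assumes only that the baseline Katz score is meant, which is the natural reading because it is in the start-of-study questionnaire.

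**What to change.** Replace the sentence on the main comparison with wording such as: *The main analysis includes every consenting respondent in both arms who meets the section 4.2 criteria, with an ISAR-PC score of 2 or more on the baseline questionnaire, analysed by the allocation of the practice, whatever the baseline Katz-ADL score and whatever care was received.*

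Replace the sentence that makes baseline adjustment conditional with a fixed one: *The mixed model for the primary outcome adjusts for the baseline Katz-ADL score.* State that Katz is not used to select patients.

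The cost is two sentences in section 9. Both scores are already collected at baseline in both arms, so no visit, form or extra patient is needed. The set would include at-risk people who decline the assessment or the care plan, which the intention-to-treat commitment already implies.

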**4.4 Sample size calculation**

The smallest difference with meaningful clinical relevance was determined at 0.5 points on the Katz-ADL15 (primary endpoint). Based on data from the pilot, this would represent a small effect size only (Cohen’s effect size of 0.20).

In this study, the intervention takes place at the level of the general practice, so this is also the unit of randomisation (cluster). Using a two-sided alpha of 0.01 and power of 90% (to keep the chances of spurious associations from multiple comparisons to a minimum) and assuming a design-effect of 1.08, in total 850 elderly people would need to receive both CGA and follow-up care. To allow for a drop-out rate of 40% (including patients who do not want treatment for identified problems, and patients who withdraw or die in the course of the study), in total around 1418 elderly people will have to receive CGA at the start of the intervention.

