**7.2 Randomisation, blinding and treatment allocation**

This is an cluster randomized controlled trial in the Netherlands, comparing regular care as control condition with a nurse led, multi-component intervention directed at geriatric problems as the experimental condition. Whereas randomization takes place at GP level, interventions take place at the individual level on the basis of identified geriatric problems. A pre-randomization procedure will be followed to allow for the allocation of a practice nurse to the intervention practices. This requires a few months of preparation, during which the nurses will take part in a specialized elderly training program and logistical preparations will be made regarding necessary consultation rooms and equipments. The randomisation procedure will be website-based, using permuted blocks (maximum block size of 4) and stratified by median number of patients (1) and social status score (2) in each GP practice.

Patients in practices randomized to the control condition receive care as usual according to the current guidelines for Dutch general practice. At baseline, all patients will receive a postal questionnaire to assess their overall risk on functional loss. In the intervention practices, patients with increased risk profiles will be asked to participate in further geriatric assessments and follow-up through an integrated care and treatment plan.

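### Baseline adjustment of the primary Katz-ADL analysis is left to observed imbalance; baseline Katz-ADL should always be in the model

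*Protocol*

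**What the plan says.** Section 9 specifies the primary model only in outline: "difference between these scores will be analyzed using a linear mixed, multilevel model", with patients nested within GPs. No fixed effects are listed. The next sentence sets the rule for baseline: "If necessary, we will adjust the effect size for baseline imbalance".

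Three other places bear on it:

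- Just before the model, section 9 says: "The main analysis focuses on a comparison of patients with a similar risk profile (based on ISAR-PC and Katz-ADL scores in both groups"). It does not say whether this is done by restriction, matching or covariates.
- Section 7.1 defines the endpoint: "The primary outcome measure is the level of (instrumental) activities of daily living (baseline-12 months"). This can be read as a 12-month score or as a change from baseline.
- Section 7.3 lists, for both arms at the start: "Postal questionnaires (i.e. ISAR-PC, Katz-ADL, MDS), along with study information and postponed informed consent". Baseline Katz-ADL is therefore available by design.

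Section 7.2 says randomisation is "stratified by median number of patients (1) and social status score (2) in each GP practice". Section 9 neither includes nor excludes these two factors.

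**The concern.** The sentence is a stated rule, and it makes the form of the primary estimate depend on the data. Imbalance can be judged only once baseline values are compared by arm. Nothing says what counts as imbalance, who judges it, or whether that happens before outcomes are known. Section 11.1 adds that the investigators handle the data and that one project leader has access to the randomisation code. Two defensible primary results could then exist, one adjusted and one not.

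The second cost is precision. The baseline value of the outcome is usually among its strongest predictors, and using it only on demand may leave the less precise analysis as the default. Section 4.4 chose a two-sided alpha of 0.01 to limit spurious findings; an open choice of analysis works against that aim.

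**Working it through.** **Inputs.** From section 4.4: difference 0.5 points, standardised effect 0.20 (so SD = 0.5/0.20 = 2.5), two-sided alpha 0.01, power 90%, design effect 1.08, and 850 people. From section 7.2: 21 practices, 1:1. The correlation r between baseline and 12-month Katz-ADL is not given; I assume 0.3 to 0.8. I take the SD of 2.5 as that of a single score, which the protocol does not state.

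**1. The plan's own figure.** n per arm = 2(2.576 + 1.282)²/0.20² = 744. Times 1.08 gives 804 per arm, about 1,607 in both arms. The stated 850 is not reproduced exactly under either reading. If it is one arm, as the flow chart in section 5 shows, power is 91.8%. If it is the total, as section 4.4 words it, power is 59%. Which is meant is a separate question; both readings are carried below.

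**2. Variance factors**, relative to the 12-month score alone:

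- 12-month score alone: 1
- change score: 2(1 − r)
- baseline-adjusted: 1 − r²

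Adjusted against change is (1 − r²)/[2(1 − r)] = (1 + r)/2. For r between 0 and 1, adjustment beats both alternatives.

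**3. Required n per arm** (744 × 1.08 × factor):

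| r (assumed) | 12-month score | Change score | Baseline-adjusted | Saving vs 12-month score | Saving vs change score |
|---|---|---|---|---|---|
| 0.3 | 804 | 1,125 | 732 | 9% | 35% |
| 0.5 | 804 | 804 | 603 | 25% | 25% |
| 0.7 | 804 | 483 | 410 | 49% | 15% |
| 0.8 | 804 | 322 | 290 | 64% | 10% |

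**4. What an adjust-if-imbalanced rule does.** Simulation of 21 practices (10 against 11) with 81 patients each (850/10.5), ICC 0.001 (0.08/80), a practice-level t-test at 0.01, and r treated as known. The trigger is assumed: adjust when a baseline test gives p < 0.05.

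| | r = 0.5 | r = 0.7 | r = 0.8 |
|---|---|---|---|
| Type I error, always adjust | 0.010 | 0.010 | 0.010 |
| Type I error, rule (default 12-month score) | 0.008 | 0.0055 | 0.004 |
| Type I error, smaller p of adjusted and unadjusted | 0.016 | 0.018 | 0.019 |
| Power, rule (default 12-month score) | 86% | 86% | 87% |
| Power, rule (default change score) | 86% | 98% | 99.9% |
| Power, always adjust | 95% | 99% | >99.9% |

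Taking the smallest p among the 12-month, change and adjusted analyses gives a type I error of 0.022 to 0.023. With 40 patients per practice and ICC 0.002 (850 read as the total), power under the rule with the 12-month default is about 50% at each r, against 65%, 84% and 95% when always adjusting.

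**5. The strata.** Both are practice-level, so they can remove at most the between-practice part of the variance: 1 − 1/1.08 = 7.4%. They cost two practice-level degrees of freedom out of 21 − 2 = 19.

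**The case against.** The strongest reply is that baseline Katz-ADL already has a role. The similar-risk-profile sentence names it, and a change score uses it by construction. That is fair as far as it goes, but neither reading fixes it as a covariate. Restriction to at-risk patients leaves baseline unadjusted within that group. Covariate adjustment would make the conditional sentence redundant or contradictory. A change score is still less precise than adjustment.

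A second reply is that covariate lists belong in the SAP, which is not shown. That disposes of any complaint about silence, but not of a rule the protocol itself states.

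A third is that the trial was sized without visible reliance on baseline adjustment and, if 850 is one arm, already exceeds 90% power on the protocol's formula. This stands: always adjusting is an improvement, not a rescue.

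Some stronger readings are not supported:

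- *The rule inflates type I error.* Applied mechanically it is conservative. Inflation needs a choice made after seeing results, which the text permits by silence but does not prescribe.
- *The strata are left out, and this makes the analysis data-dependent or the test anti-conservative.* Section 9 is silent on them. Omitting them creates no dependence on the data and, where they are prognostic, tends to make the standard error too large.
- *The same covariates belong in every secondary model.* Some of these are logistic, where adjustment changes the odds ratio being estimated, and baseline Katz-ADL is not the baseline of the quality-of-life or ALDS scores.

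**Conclusion.** The point holds for baseline Katz-ADL in the primary model. Section 9 makes adjustment conditional without trigger, covariate or timing, so the form of the primary estimate is decided after data are seen, and the default may be the less precise one.

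The size rests on two things the protocol does not settle: r, and whether the default outcome is the 12-month score or the change. For assumed r of 0.5 to 0.8 the variance reduction is 25% to 64% in the first case, and 25% falling to 10% in the second. The type I error and power figures also rest on the assumed p < 0.05 trigger and the ICC implied by the design effect. The stratification factors are a minor addition, worth at most about 7% of variance on the protocol's own design effect.

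**What to change.** Replace the conditional sentence in section 9 with:

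> The primary linear mixed model of 12-month Katz-ADL will include baseline Katz-ADL as a fixed effect whatever the observed balance.

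This also removes the ambiguity between 12-month score and change: once baseline is a covariate, both give the same treatment coefficient.

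The two randomisation strata (practice size and social status score) can be added as fixed effects. The choice should be stated in advance, since the expected gain is small and the cost is two of about 19 practice-level degrees of freedom.

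For baseline Katz-ADL the cost is wording only, because it is already collected in both arms. Covariates for the secondary models should be decided outcome by outcome.

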5.0 STUDY DESIGN

**5.1 Study design**

A multicenter, cluster randomized clinical trial at the level of the General Practitioner (GP) comparing a pro-active, multi-component (multidisciplinary and multidimensional) intervention, coordinated by a Health Care Nurse (HCN) with care as usual.

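### The supplementary log-rank test, the only time-to-event test named, ignores practice randomisation, and the randomised unit is called both GP and practice

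*Protocol*

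**What the plan says.** **Survival.** Section 9 first sets out a linear mixed multilevel model for the Katz-ADL score, because "patients are ‘nested’ within their GPs". It then extends that approach: "The same (linear and logistic) multi-level approach will be used with regard to the secondary outcome parameters, including survival rates". Only after this does it add the test at issue: "Survival data will be additionally analyzed using Kaplan-Meier survival curves and the log-rank test". No clustering adjustment is attached to that last sentence. The section asks for 99% confidence intervals in all analyses, and the Summary lists overall mortality among the secondary outcomes.

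**Randomised unit.** The sections differ.

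- General practice: section 4.4 says "the intervention takes place at the level of the general practice, so this is also the unit of randomisation (cluster"). The table in 7.3 has "Pre-randomisation at the level of GP practices". The end of 7.2 speaks of the equivalent of 21 GP practices allocated 1:1, and Figure 1 shows 10 or 11 practices per arm.
- GP: the Summary and 5.1 place the cluster randomisation at the level of the General Practitioner, and 7.2 has "Whereas randomization takes place at GP level".

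Section 7.2 itself also refers to practices randomised to the control condition, so both terms occur within one section. The protocol does not say how many GPs a practice has.

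**The concern.** Patients in one practice share an allocation and may have correlated mortality. The log-rank variance leaves that correlation out, so the standard error is too small and the test rejects too often. The plan gives clustering as its reason for multilevel models and then names, for time to death, a test that has no place for it. Because the multilevel approach is described as linear and logistic, the log-rank result is the only one that uses the timing of deaths. Nothing says which result governs if the two disagree.

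The unit matters because a random effect protects the treatment comparison only if it sits at the level that was randomised. With two names for that level, an analyst could place it one step too low.

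**Working it through.** **Inputs from the protocol.** Two-sided alpha 0.01 and design effect 1.08 (4.4); 10 or 11 practices per arm, so 10.5 on average, and about 2835 respondents per arm of whom about half are at increased risk (Figure 1).

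**Assumptions.** The protocol gives no intracluster correlation (ICC), no mortality rate and no number of GPs per practice. The ranges used are ICC 0.005 and 0.01, 6% one-year mortality, and 1 to 4 GPs per practice.

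**Cluster size.** 2835 × 0.5 = 1417.5, which reproduces the 1418 in Figure 1. 1418 / 10.5 = 135 at-risk patients per practice.

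**True level when clustering is ignored.** DE = 1 + (m − 1) × ICC, and true two-sided level = 2 × [1 − Φ(2.5758 / √DE)].

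| Case | DE | 2.5758 / √DE | True level |
|---|---|---|---|
| Plan's own design effect | 1.08 | 2.479 | 1.3% |
| ICC 0.005, m = 135 | 1 + 134 × 0.005 = 1.67 | 1.993 | 4.6% |
| ICC 0.01, m = 135 | 1 + 134 × 0.01 = 2.34 | 1.684 | 9.2% |

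In the first row √1.08 = 1.039, so the standard error is about 4% too small and a nominal 99% interval covers about 98.7%. That row assumes that the design effect, set for the Katz score, carries over to mortality. With m = 135 it implies an ICC of 0.08 / 134 = 0.0006.

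**Simulation of the log-rank test itself.** 22 practices of 135 patients, 12 months' follow-up, 6% mortality, no treatment effect, log-normal practice frailty, 2000 runs. The formula column uses ICC ≈ v × 0.06 / 0.94, where v is the variance of the log frailty.

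| v | Approximate ICC | DE | Formula | Simulated |
|---|---|---|---|---|
| 0 | 0 | 1 | 1.0% | 0.70% |
| 0.01 | 0.0006 | 1.09 | 1.3% | 1.45% |
| 0.05 | 0.0032 | 1.43 | 3.1% | 3.0% |
| 0.10 | 0.0064 | 1.86 | 5.9% | 6.45% |

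The Monte Carlo standard error near 1% is √(0.01 × 0.99 / 2000) = 0.22 percentage points, so formula and simulation agree well enough for this purpose.

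**The mixed model.** If the GP is the randomised unit, or each practice has one GP, a random effect for GP is at the right level and the test holds 1.0%. Now suppose instead that a practice has g GPs, all correlation is at practice level, and only a GP effect is fitted. The variance is then understated by [1 + (m − 1) × ICC] / [1 + (m/g − 1) × ICC], and this ratio replaces DE in the formula above.

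- Design effect 1.08 (ICC 0.0006), g = 2 to 4: 1.15% to 1.23%.
- ICC 0.01, g = 2: 2.340 / 1.665 = 1.405, level 3.0%.
- ICC 0.01, g = 4: 2.340 / 1.328 = 1.763, level 5.2%.

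**The case against.** The strongest reply is that survival already has a cluster-aware analysis. The sentence before the log-rank test brings survival rates under the multilevel approach, and the word additionally marks the log-rank test as a supplement. This stands: a reader might infer that mortality is tested only by a method blind to clustering, and the text says otherwise. It does not make the supplementary test valid, however, and the multilevel analysis as described does not use event times.

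A second reply is that the only documented input, the design effect of 1.08, puts the error at 1.3% against 1%, and that the larger figures rest on ICCs the protocol does not give. This also stands. In turn, the protocol offers no ICC that would show 1.08 to be right for mortality.

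A reader might also infer that the primary Katz analysis and the 99% intervals in general are too narrow because patients are nested in GPs while practices are randomised. The documents do not support that. They use GP and GP practice interchangeably for the cluster, so the nesting may simply name the randomised unit. The 4.6% and 9.2% figures describe an analysis with no cluster adjustment at all, which the Katz model is not.

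**Conclusion.** The concern holds for the log-rank test. As written, it does not keep its nominal 1% level in a trial that allocates practices. The excess is small at the plan's own design effect (1.3%). It becomes material (4.6% to 9.2%) at ICCs of 0.005 to 0.01 with 135 at-risk patients per practice; those ICCs are assumptions. The consequence is confined to the log-rank p-value and any unadjusted intervals around the Kaplan-Meier curves.

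The two names for the randomised unit are a real inconsistency that should be settled. For the primary Katz analysis this is a matter of wording unless practices hold several GPs and no practice-level term is fitted, and neither condition can be read from the protocol.

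**What to change.** 1. In section 9, replace the log-rank test with a cluster-adjusted log-rank test, or with a Cox model that has practice-level frailty or practice-clustered robust variance. Keep the Kaplan-Meier curves as description.
2. State which survival result governs if the multilevel and time-to-event analyses differ.
3. Name one randomised unit in the Summary, 4.4, 5.1, 7.2, 7.3 and section 9, and place the random effect of the mixed model at that unit. If it is the practice and practices hold several GPs, a GP term may be added below the practice term but should not replace it.

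Further detail, such as small-sample corrections for 21 clusters, can be left to the statistical analysis plan. The cost is a few changes of wording and a different model call. The survival intervals may widen somewhat: by about 4% on the standard-error scale if the design effect is 1.08, and by more if clustering is stronger. The design and the data collection do not change.
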